## Primary outcome measures

The primary outcome will be change in a person’s self-efficacy measured by the GSE [32]. The GSE is a reliable (*α* = 0.76 to 0.90), validated, ten-item unidimensional self-report scale used to assess self-efficacy within general adult populations. The scale conceptualises self-efficacy as a person’s perceived ability to cope and adapt in the face of both daily hassles and more stressful life events. Respondents indicate how much a given item applies to them from 1 (not at all true) to 4 (exactly true), with total possible scores of 10–40 (higher scores indicate greater self-efficacy). The scale was originally designed to assess change occurring over the course of a trial and is also used in CMO contexts as an indicator of client well-being. This tool will be used to inform intervention efficacy for participants at baseline, 3 months post-baseline, 6 months post-baseline, and 9 months post baseline. For all measures taken at multiple time points, the comparison between care as usual (baseline) and post-intervention (3 months post-baseline) will be of primary importance, whilst following time points will inform the longevity of any intervention-related effects.

All baseline measures, including the GSE, will be administered as a questionnaire by a practice nurse following screening and consent procedures. During the final session of peer support, the peer worker will assist the participant with completing the 3-month post-baseline measures. All further follow-up measures will be administered as a questionnaire either through REDCap or a telephone call from study staff depending on participant preference.

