**Methods:**

This stepped-wedge cluster randomised controlled trial (RCT) aims to evaluate a lived experience peer support intervention for accessing mental health care in primary care (PS-PC). Four medical practices across Australia will be randomly allocated to switch from control to intervention, until all practices are delivering the PS-PC intervention. The study will enrol 66 patients at each practice (total sample size of 264). Over a period of 3–4 months, 12 h of practical and emotional support provided by lived experience peer workers will be available to participants. Scale-based questionnaires will inform intervention efficacy in terms of mental health outcomes (e.g., self-efficacy) and other health outcomes (e.g., healthcare-related costs) over four time points. Other perspectives will be explored through scales completed by approximately 150 family members or carers (carer burden) and 16 peer workers (self-efficacy) pre- and post-intervention, and 20 medical practice staff members (attitudes toward peer workers) at the end of each study site’s involvement in the intervention. Interviews (*n* = 60) and six focus groups held toward the end of each study site’s involvement will further explore the views of participants, family members or carers, peer workers, and practice staff to better understand the efficacy and acceptability of the intervention.

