## Randomisation

The four practices will be randomly allocated by the study statistician to receive the standardised PS-PC intervention until all four sites have implemented it. Timing of allocation will depend on the relative needs of the practices and peer worker providers (e.g., staffing, leave arrangements, time of year). At the initialisation of each wedge, staff leaders at the relevant practice site will champion the practical implementation of the PS-PC, beginning with recruitment strategies. All participants will receive usual care, plus the addition of peer support when their study site switches to the PS-PC intervention. Due to the trial’s specific nature, neither randomisation nor blinding of participants will take place. Participants have the freedom to withdraw from the intervention at any time upon their request.

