**Fig. 3 Fig3:**
[figure not shown]
Schedule of enrolment, intervention, and assessment (SPIRIT Figure)

A summary of the evaluation schedule, underpinned by the RE-AIM framework is provided in Table 1. Routinely collected data including demographics and diagnosis details will be recorded (with consent) by practice staff through chart auditing the GP records of prospective participants. At baseline and during the final peer support session, participants will have the option of completing data collection forms on paper, using iPads available at each study site or using another digital device. Data from paper forms will be entered into the REDCap database by the practice manager, practice nurse, or research officer. Paper data collection forms will be audited against online data at the end of the study for accuracy and completeness. All data collection forms are available on request.

**Table 1 Tab1:** Evaluation schedule with RE-AIM framework domains

RE-AIM Domain	Measure	Evaluation process
Reach	Number of people living with mental health conditions referred to the project	Analysis of routinely collected process data
	Characteristics (i.e., age, gender, diagnosis, treatment) of those who consent to participate vs. those who did not	
Effectiveness		
*Primary*	Participant self-efficacy (GSE)	Collected at enrolment (-t_1_) or baseline (t_0_) 3, 6, 9 months (t_1_ to t_3_) post-baseline
*Secondary*	Patient psychological distress (K10) Participant personal recovery (RAS-DS) Cost-effectiveness (EQ-5D-5L)	
	Family member or carer burden (BSFC-s) Peer worker self-efficacy (GSE)	Collected pre- (t_0_) and post-intervention (t_1_)
	Participant satisfaction with service (YES^a^) Practice staff attitudes towards peer workers^b^ Participant service use costs^c^ Perceived effectiveness of trial^b^	Collected post-intervention (t_1_) only
Adoption	Perspective of participants, family members and carers, peer workers, and practice staff	Semi-structured interviews and focus groups Analysis of routinely collected process data
Implementation	Frequency and content of participant-peer worker encounters	
Maintenance	Feedback from participants, family members and carers, peer workers, and practice staff	

^a^Short-form adjusted for CMOs

^b^Measure (Likert scale) developed for the study, in (TFA)

^c^Self-report questionnaire of service use and associated costs

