## Statistical methods

Independent sample *t*-test and standard Chi-square test for association with continuity correction will compare participant characteristics during usual care with those during mid- and post-intervention. Multivariate multilevel mixed-effects models will be used to examine changes in outcome measures between pre-intervention baseline and post-intervention follow-up over time (6, 12, and 18 months) including interactions between pre-intervention baseline and post-intervention follow-up over time. The comparison between care as usual (baseline) and post-intervention (3-months post-baseline) will be of primary importance, whilst subsequent time points will inform the longevity of any intervention-related effects. This analytical strategy is selected due to the hierarchical nature of the data, where participants are nested within practices. Linear models will be used for continuous outcomes (i.e., GSE, K10, RAS-DS, YES, EQ-5D-5L, TFA) and logit models for binary outcomes (e.g., demographics, diagnosis, etc.). The two-sided test will be performed for all analyses, 95% confidence interval reported, and level of significance set at *p* < 0.05. All analyses will be performed using Stata software version 16.1 and R version 4.1.1. Responses on the EQ-5D-5L integrated with survival curves will be integrated estimate quality adjusted life years using the quality-adjusted survival analysis method. Participant self-reported service use during usual care will be compared with those during and post-intervention to determine within-trial incremental costs and trial effectiveness. Where there is missing data, intention-to-treat protocol will be followed for all participants who receive peer support, where baseline information is available. If there is a significant amount of missing data (missing at random), multiple imputation will be used.

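### The comparison named as primary is each participant's own baseline against 3 months, an uncontrolled before-after change that conflicts with the stepped-wedge controlled design and its sample size

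*Protocol article*

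**What the plan says.** The Abstract describes the design: "Four medical practices across Australia will be randomly allocated to switch from control to intervention, until all practices are delivering the PS-PC intervention". Under Primary outcome measures, "The primary outcome will be change in a person’s self-efficacy measured by the GSE", taken at baseline and 3, 6 and 9 months after it. The same section fixes the main comparison: "the comparison between care as usual (baseline) and post-intervention (3 months post-baseline) will be of primary importance". Statistical methods says it again: "The comparison between care as usual (baseline) and post-intervention (3-months post-baseline) will be of primary importance". The later time points are there to show how long any effect lasts.

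The mixed model is described as examining "changes in outcome measures between pre-intervention baseline and post-intervention follow-up over time (6, 12, and 18 months"), and the stated reason for it is that participants are nested within practices. The intention-to-treat rule for missing data covers participants who receive peer support and have baseline information.

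On timing, Randomisation says that when a wedge starts, staff leaders at that practice "will champion the practical implementation of the PS-PC, beginning with recruitment strategies". It also says "Timing of allocation will depend on the relative needs of the practices and peer worker providers (e.g., staffing, leave arrangements, time of year"). Table 1 (Data collection) gives the pre-intervention measure as "Collected at enrolment (-t_1_) or baseline (t_0").

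Sample size takes its effect from a randomised trial of peer support against usual care: a between-group difference of 1.77 points (95% CI 0.02 to 3.53). It plans on the upper limit, 3.53.

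**The concern.** A stepped wedge identifies the treatment effect by comparing practices that have switched with practices still in usual care over the same calendar period. The comparison named as primary does something else. It sets a person's score before peer support against the same person's score 3 months later. Everyone in that contrast is untreated at time zero and treated at 3 months, so time since enrolment and exposure are the same variable. A term for one cannot be separated from a term for the other.

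Participants are attenders whom GPs think may benefit, or people who put themselves forward from the waiting room. Some improvement under ordinary GP care is therefore plausible, and all of it would enter the estimate. The stated objective is efficacy, and the Discussion says that a positive result may support inclusion in the Medicare Benefits Schedule. A before-after change cannot carry that claim.

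**Working it through.** **1. What the sample size was built for.** Inputs from Sample size: SD 7.2, ICC 0.01, difference 3.53, one-sided 0.05, power at least 80%, 10% attrition, 66 per practice, 264 in total. My assumption: 4 practices, 5 periods, one switch per step, equal cells, different people in each cell, fixed period effects and a random practice effect.

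- 12 people per cell gives SE 1.42.
- 3.53 / 1.42 = 2.49, and 2.49 − 1.645 = 0.84, so one-sided power is 80.0%.
- 12 × 5 = 60 per practice and 60 × 4 = 240 evaluable. 60 × 1.1 = 66 per practice and 66 × 4 = 264. This matches the stated figure. (Dividing by 0.9 gives 67 per practice.)

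In that layout 10 of the 20 cells are usual-care cells. Several parallel-group calculations that were tried did not return 264. So the stated size is consistent with a period-adjusted stepped-wedge contrast against usual care, although the article does not print the layout.

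**2. What the named primary comparison estimates.** For n pairs with equal SDs and within-person correlation r:

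expected estimate = true effect + untreated change over 3 months

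SE = SD × √(2(1 − r)/n)

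With SD 7.2 and n = 240:

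| r (assumed) | SE |
|---|---|
| 0.3 | 7.2 × √(1.4/240) = 0.550 |
| 0.5 | 7.2 × √(1.0/240) = 0.465 |
| 0.7 | 7.2 × √(0.6/240) = 0.360 |

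These are far below 1.42 because the before-after contrast estimates neither a period effect nor a usual-care comparison.

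**3. Rejection rate with no true effect.** For an untreated gain g and a two-sided 0.05 test, the rate is Φ(g/SE − 1.96) + Φ(−g/SE − 1.96). Example: g = 1 and r = 0.5 give 1/0.465 = 2.15, and Φ(0.19) ≈ 0.58.

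| Untreated gain g (assumed) | r = 0.3 | r = 0.5 | r = 0.7 |
|---|---|---|---|
| 0.5 point | 15% | 19% | 28% |
| 1 point | 44% | 58% | 79% |
| 1.5 points | 78% | 90% | 99% |

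With g = 0 the rate is 5%, as it should be. The gains and correlations are assumptions, since the document gives neither. The bias itself equals g at any value of r.

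**4. What the randomised contrast would deliver.** In the layout of step 1, two-sided power at 240 evaluable is Φ(2.49 − 1.96) ≈ 70%. Reaching 80% two-sided takes about 16 per cell. That is 16 × 5 × 4 = 320 evaluable, or 352 (× 1.1) to 356 (÷ 0.9, rounded up) recruited. This treats each cell as different people. Repeated measures on the same people may do better, which is why the calculation should be redone for the actual schedule.

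**The case against.** The strongest reply is that this is a condensed article without its analysis plan, and that a usual-care phase is hinted at. Randomisation says that all participants have usual care and gain peer support when their site switches. Statistical methods compares participant characteristics during usual care with those during and after the intervention. The 6, 12 and 18 months in the model sentence could be calendar steps, although they do not match the 3, 6 and 9 months given for the GSE. Figures 1 and 3, which would show flow and schedule, are not in the text at hand.

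Much of this stands, and it rules out some stronger readings:

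- A reader might infer that nobody contributes untreated follow-up and that the randomised order goes unused. The text does not say so. It shows that no usual-care GSE re-measurement is stated, and that the comparison named as primary would not use one.
- A reader might count the lack of a named step term or exposure indicator as an omission. Exact model terms can be left to the analysis plan. What is open to criticism is the contrast that the article itself fixes, twice.
- A reader might infer that practice needs decide which practice switches first, and hence that the order is biased. The article says that the statistician allocates practices at random and that needs affect timing. No bias from a needs-driven order can be derived from that.
- The choice in Table 1 between enrolment and baseline is weak evidence of a single pre-measure for the GSE. The cell may also cover the K10, which is taken at screening.
- Excluding people with a K10 above 40 may reduce regression to the mean. It does not remove natural recovery.

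None of this alters the comparison that both sections declare to be primary.

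**Conclusion.** The point holds. The comparison of primary importance is a within-person before-after change with the baseline standing in for usual care. It conflicts with the stepped-wedge controlled design and with a sample size built on a between-group difference. Any untreated change is added in full to the estimate. Under the assumptions shown (SD 7.2, 240 pairs, r 0.3 to 0.7), a trial with no true effect would be declared positive in about 15-28%, 44-79% or 78-99% of cases for untreated gains of 0.5, 1 or 1.5 points. How large the untreated gain will be is unknown, so a false positive is a conditional risk and not a forecast. The conflict between the named comparison and the design does not depend on those assumptions.

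**What to change.** 1. Make the primary effect GSE under peer support versus concurrent usual care. Estimate it with a mixed model containing calendar step, time since enrolment and an intervention indicator set by the practice's randomised switch date, with random practice and participant effects. Keep the baseline-to-3-month change as a descriptive result.
2. At practices not yet switched, enrol one step ahead and take the GSE at both enrolment and pre-intervention baseline, so that untreated change is observed. If the full schedule already does this, say so.
3. State that the order of the remaining practices is fixed by the random draw, and that practice and provider needs may move dates only.
4. If usual-care data cannot be obtained, report the primary result as an uncontrolled before-after change and drop the controlled-efficacy claim.

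The cost is one extra ten-item questionnaire and earlier recruitment at waiting practices, plus a wider standard error than the before-after contrast. The power statement must be recalculated for two-sided testing: about 70% for 3.53 points at 240 evaluable in the cross-sectional layout above, so it cannot be assumed that no extra participants are needed. Recruitment began in November 2023, so waiting-period data may be out of reach at any practice that has already switched.

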**Fig. 2 Fig2:**
[figure not shown]
Intervention stages and flow of care

The initial meeting between the participant and peer worker will provide an opportunity to refine and mutually agree on the support plan. Support may entail emotional and practical assistance, phone calls, home visits, community linkage, and sharing of strategies to enhance lifestyle behaviour (e.g., social connection, physical activity, stress management) to build self-efficacy and self-care and to set recovery goals.

Peer workers will provide 8–12 h of support per participant over approximately 2–3 months, with the option to extend for 2–3 months if needed. If desired, participants may also cease receiving peer worker support sessions prematurely, if they feel they have gained sufficient benefit from these sessions. At the completion of the intervention, the peer worker and participant will identify supports that are relevant and available and the peer worker will link the participant with those supports. The peer worker will provide a summary of trial activities to the participant and their GP. This is intended to be used for discussion in a primary care appointment to facilitate ongoing continuity of care.

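### The primary 3-month GSE is completed with the treating peer worker's help at the final support session, and its timing follows that session rather than a fixed date

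*Protocol article*

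**What the plan says.** The Primary outcome measures section describes the GSE as a "ten-item unidimensional self-report scale used to assess self-efficacy within general adult populations". It says that, for repeated measures, "the comparison between care as usual (baseline) and post-intervention (3 months post-baseline) will be of primary importance", and Statistical methods repeats that priority. The same section sets three routes for collecting the scale:

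- Baseline: "All baseline measures, including the GSE, will be administered as a questionnaire by a practice nurse following screening and consent procedures".
- 3 months: "During the final session of peer support, the peer worker will assist the participant with completing the 3-month post-baseline measures".
- 6 and 9 months: "All further follow-up measures will be administered as a questionnaire either through REDCap or a telephone call from study staff", according to participant preference.

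Data collection lets participants choose paper, an iPad or another device at baseline and at the final session. Randomisation states that participants are not blinded.

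On timing, Table 1 labels the first follow-up as 3 months after baseline. The Intervention section has support running "over approximately 2–3 months, with the option to extend for 2–3 months if needed", and also lets participants stop sooner if they feel they have benefited enough. The Abstract gives a different length: "Over a period of 3–4 months, 12 h of practical and emotional support provided by lived experience peer workers".

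On the K10, Secondary outcome measures names a GP or study nurse as administrator at screening and carries the sentence on to 3, 6 and 9 months. Primary outcome measures hands the 3-month measures to the peer-assisted final session without exception.

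**The concern.** The route of administration changes exactly across the primary contrast, and at its second point it involves the person who has just delivered the intervention. Participants know what they received, the scale is their own judgement of themselves, and the Introduction describes the peer relationship as one of mutual exchange between equals. A participant may rate themselves more favourably with that person helping than with a nurse or on a web form.

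Because a peer worker is present only once the intervention is running, assistance and exposure coincide. Neither a before–after comparison nor a comparison of control with intervention periods can separate the two. The unassisted 6-month score helps only partly, since a fall from 3 to 6 months could reflect a fading effect or the change of route.

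A second problem is that an outcome attached to the last session is taken at a time that depends on need and engagement, and someone who simply stops attending may not have it taken at all.

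**Working it through.** **1. Routes side by side (Primary outcome measures).**

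| Time point | Who is involved | Role in the primary contrast |
|---|---|---|
| Baseline | practice nurse | first point |
| 3 months | treating peer worker, final session | second point |
| 6, 9 months | REDCap or study-staff call | durability only |

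The only peer-assisted GSE is the one at the second point of the primary contrast. The choice of paper or device changes the medium but does not remove the assistance.

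**2. When the final session falls (Intervention section).** Assume support starts at baseline; any delay for matching a peer worker would add to these times.

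- Unextended: about 2–3 months, so 0–1 month before the nominal 3.
- Extended: 2 + 2 = 4 to 3 + 3 = 6 months, so 1–3 months after it. At the upper end it coincides with the 6-month measure.
- Stopped early: possibly before 2 months.
- On the Abstract's length: 3–4 months.

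**3. Scale arithmetic (illustration only).** Ten items are scored 1–4. An average rise of one category on one item is 1 point, or 1/3.53 = 28% of the difference used for power. On two items it is 2 points: 2/3.53 = 57% of that difference, and 2/1.77 = 113% of the effect observed in the source trial.

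**4. What a spurious shift could do (illustration; the shifts and correlations are assumptions).**

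The plan's own sample size was reproduced first. Inputs from Sample size: 4 practices, SD 7.2, ICC 0.01, difference 3.53, one-sided 0.05. Assumed: 5 periods, cross-sectional Hussey–Hughes variance. With 60 analysable per practice (12 per practice-period), power is 80.0%, and 60 × 1.10 = 66 per practice, or 264 in total. The stated figure is reproduced.

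Now take no true effect, a spurious shift b at the assisted assessment, and a two-sided 0.05 test as in Statistical methods:

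P(reject) = 1 − Φ(1.96 − b/SE) + Φ(−1.96 − b/SE).

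- *Simple before–after contrast.* 264 × 0.9 = 237.6, taken as 237. SE = 7.2 × √(2(1 − r)/237), which is 0.553 for r = 0.3, 0.468 for r = 0.5 and 0.362 for r = 0.7. Clustering is ignored.
- *Stepped-wedge contrast.* 237.6/4 = 59.4 per practice, or 11.88 per practice-period. σ² = 51.84 × 0.99/11.88 = 4.32 and τ² = 51.84 × 0.01 = 0.518. With U = 10, W = 30, V = 30, the variance is 4 × 4.32 × (4.32 + 5 × 0.518)/(10 × 4.32 + 30 × 0.518) = 2.03, so SE = 1.43.

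| Shift b | Before–after, r = 0.3 / 0.5 / 0.7 | Stepped wedge |
|---|---|---|
| 0.5 | 15% / 19% / 28% | 6% |
| 1.0 | 44% / 57% / 79% | 11% |
| 1.77 | 89% / 97% / 100% | 24% |

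The before–after column is relevant because the article words its primary comparison as baseline against post-intervention. The spread between columns shows how strongly the consequence depends on the contrast finally modelled.

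**The case against.** The strongest reply is that nothing here demonstrates bias. Help with the form is undefined and may be purely practical, such as handing over a tablet. Baseline is itself given by a staff member, so favourable answering need not be confined to follow-up. Both points stand: this is a possible difference in bias between two time points, and its size is unknown.

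Four stronger readings are tempting, and the documents do not support them.

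- *The score is never taken at 3 months.* Table 1 and Primary outcome measures both name 3 months, and an unextended course of about that length would meet it. What is missing is a tie to a date. The full protocol or the schedule figure, neither of which is shown, may give a window, but the stated rule still attaches the measure to the session.
- *Participants who disengage have no primary outcome.* The article does not say so. Retention and withdrawal offers a wrap-up session where relevant, and Statistical methods provides for multiple imputation. It is fair to say only that those who stop attending may lack the assessment, because no other route for the 3-month measures is described.
- *Timing and missingness also favour the intervention.* Early stoppers may be those who feel they have gained enough, and extension is for those who need more. The net direction is uncertain.
- *A plausible shift exceeds the planned effect.* The trial is powered for 3.53 points; 1.77 is the source trial's observed mean difference. A 2-point shift is below the former and above the latter.

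It is also fair to object that moving the 3-month score to REDCap or telephone leaves a mode change from the nurse-given baseline, and makes the score mid-intervention for extended participants. Both are real costs and are taken up in the fix.

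**Conclusion.** The concern holds as a risk built into the primary contrast. The protocol places the deliverer's assistance at the primary time point and nowhere else, on a self-report outcome in unblinded participants, and the effect of that assistance cannot be cleanly separated from the treatment effect afterwards. This part rests on explicit text and needs no assumption.

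The size rests on assumptions. With no true effect, an assumed 1-point shift would give a false-positive rate of 44–79% in a simple before–after contrast (correlation 0.3–0.7, clustering ignored), or about 11% in a five-period stepped-wedge contrast, against a nominal 5%. Deliverer assistance would plausibly push towards benefit, but that is not shown.

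The timing defect also holds: as written, the 3-month measure can fall anywhere from before 2 months to 6 months, with an uncertain effect on the estimate. The sample-size figure is not affected by this point. The change is needed because the defect sits on the primary outcome and cannot be repaired once the scores have been collected.

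**What to change.** 1. Collect the 3-month GSE and the other participant-reported outcomes in a stated window around 3 months after baseline, whatever the session status. Use self-completion through the existing REDCap link or a study-staff call, without the peer worker's assistance.
2. Preferably use self-completion at baseline too, so that the mode matches across the primary contrast. Otherwise state that a change from nurse to REDCap or telephone remains.
3. Collect YES and the acceptability scale by the same route after support ends. Both are now completed in the final session, and they rate the service or the intervention itself.
4. State that the primary contrast is by time since baseline. For participants whose support is extended, the 3-month score will then be mid-intervention, which changes what the current post-intervention label means.
5. Recruitment had begun when the article appeared. Date the change and record the route and date of each GSE, so that peer-assisted scores already collected can be identified and examined in a sensitivity analysis.
6. Reconcile the Abstract and the Intervention section on the length of support, and both with the assessment schedule. Reconcile Primary and Secondary outcome measures on who administers the K10 at 3 months.

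The cost is up to 264 extra contacts (one per participant) for the 3-month measures through a route already planned for 6 and 9 months, plus the later contact for YES and acceptability where it cannot be combined. Completion may be lower than with in-session collection; the documents give no figure for this. Delivery of support is unchanged.

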## Secondary outcome measures

### Efficacy

Psychological distress: The Kessler Psychological Distress Scale (K10) is a reliable (*α* = 0.93), validated, 10-item unidimensional self-report measure of participant mental distress [33] often used by clinicians as a screening tool and marker of eligibility for government-funded support services. Respondents indicate from 1 to 5 how much a given statement was true for them in the past 4 weeks with total possible scores of 10–50 (lower scores indicate less distress). The GP or a study nurse will administer the K10 to potential participants as a screening material to aid in confirming eligibility, and then at 3 months post-baseline, 6 months post-baseline, and 9 months post-baseline.Personal recovery: The Recovery Assessment Scale—Domains and Stages (RAS-DS) [18] is a reliable (*α* = 0.96), validated, 38-item multidimensional self-report measure of personal recovery designed to measure the recovery-oriented impact of services provided to participants. The scale is constructed of five domains relevant to recovery goals, with respondents indicating how much a given statement is true for them from 1 to 4. Higher scores in each domain or stage indicates areas the person feels more confident about as part of their recovery. The RAS-DS is routinely used by peer workers as a descriptive tool. This tool will be used to inform intervention efficacy for participants at baseline, 3 months post-baseline, 6 months post-baseline, and 9 months post-baseline.Satisfaction with service: The Your Experience of Service (YES) is a descriptive short-form (21-item) version of the Australian YES [34] tailored to evaluating CMOs. The YES is used in evaluating services delivered by government and non-government healthcare providers in Australia. Respondents indicate their experiences from 0 to 5 across three areas (higher score indicates more satisfaction with a service). The measure then prompts responses to open-ended questions for further information. This measure will be completed during the participant’s final session.

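### The 3-month measures, including the primary GSE score, are tied to the final support session, but support can be extended to about 4–6 months, so for extended participants the two timing rules conflict

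*Protocol article*

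**What the plan says.** The Primary outcome measures section and Table 1 (Data collection) give a calendar schedule for the GSE: baseline, then "3, 6, 9 months (t_1_ to t_3_) post-baseline". The same section states that "the comparison between care as usual (baseline) and post-intervention (3 months post-baseline) will be of primary importance", and Statistical methods repeats this.

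The Primary outcome measures section also gives a rule based on an event: "During the final session of peer support, the peer worker will assist the participant with completing the 3-month post-baseline measures". Data collection agrees with it: "At baseline and during the final peer support session, participants will have the option of completing data collection forms".

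The Intervention section sets support at about 2–3 months, "with the option to extend for 2–3 months if needed". It also allows the course to be shortened: "participants may also cease receiving peer worker support sessions prematurely", when they feel they have benefited enough. The abstract gives 3–4 months and mentions no extension.

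No text shown says which rule governs when the final session is not near month 3.

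**The concern.** The two rules agree only if support ends at about month 3. The extension breaks that agreement for the score on which the main comparison rests. K10, RAS-DS and EQ-5D-5L share the same 3-month point, so they are affected too.

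Under the final-session rule, a participant who needs more support is measured later. The time since baseline then depends on the participant's own course, and scores with the same label come from different follow-up times. Under the calendar rule the date is fixed, but an extended participant is measured during support, which does not fit the label of a post-intervention score. Each rule could be defended alone. Stating both leaves the meaning of the main comparison unsettled for extended participants.

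**Working it through.** **Inputs**
- Length of support *D*: 2–3 months without extension; (2–3) + (2–3) = 4–6 months with it (Intervention); 3–4 months (Abstract, Methods).
- Nominal time of the primary score: month 3. Next assessment: month 6 (Table 1).
- Lag *L* from baseline to the start of support: not stated. Zero is assumed, with 1 month as a sensitivity case.

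**Formulas**
- Month of the final session = *L* + *D*.
- Departure from the nominal date = *L* + *D* − 3.
- Gap to the 6-month assessment = 6 − (*L* + *D*).

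**Final-session rule**

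| Case | Final session (month) | Departure from month 3 | Gap to month 6 |
|---|---|---|---|
| No extension, *L* = 0 | 2–3 | −1 to 0 | 3–4 months |
| Extended, *L* = 0 | 4–6 | +1 to +3 | 0–2 months |
| Abstract's 3–4 months, *L* = 0 | 3–4 | 0 to +1 | 2–3 months |
| No extension, *L* = 1 | 3–4 | 0 to +1 | 2–3 months |
| Extended, *L* = 1 | 5–7 | +2 to +4 | 1 month before to 1 month after |

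The nominal month 3 is reproduced exactly only for a 3-month course that starts at baseline and is not extended. With no lag, planned courses spread the score over 6 − 2 = 4 months, but that takes the shortest unextended and the longest extended course together. After a 3 + 3 month course, the 3-month and 6-month scores fall at the same time.

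**Calendar rule.** At month 3 an extended participant still has 4 − 3 = 1 to 6 − 3 = 3 months of support to come.

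**Number affected.** The share who extend is not given, so this cannot be calculated. For scale only: 264 × 0.9 = 237.6, about 238 participants after the planned 10% attrition. An assumed share of 10%, 30% or 50% would be about 24, 71 or 119 scores. The sample size calculation does not depend on this point.

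All bounds are approximate, because the protocol describes the length of the initial course as approximate.

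**The case against.** The strongest reply is that the plan has one end-of-support assessment with a nominal 3-month label. Several statements fit this: the score is called post-intervention, Table 1 uses the same time code (t1) for measures collected after the intervention, and two sections place collection at the final session. On that reading the label is merely imprecise. This stands for unextended courses, where a month either way is ordinary visit variation. It does not settle the extended ones, because 3 months post-baseline is also listed as a schedule point and a long course carries the score to the 6-month assessment.

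A second reply is that Figs 2 and 3 are not shown and that the article condenses a fuller protocol, where visit windows may be set. A missing window is indeed no finding. The point here is a conflict between two collection rules that are both stated. An analysis window could exclude or relabel a late score, but it could not supply a month-3 score that was never collected.

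Third, the abstract's 3–4 months makes the delay small. That is correct if 3–4 months is the true total. The Intervention section is the more detailed source, however, and it allows the extension.

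A reader might go further and infer that the primary result is biased in a known direction, that many scores are affected, or that early stoppers will be measured well before month 2. The document supports none of these. It gives no extension rate and no basis for a direction. It also does not say that an early stopper's last session would be recognised in advance and used for the forms.

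**Conclusion.** The conflict is real but limited. For extended participants the main GSE score is either about 1–3 months late, reaching the 6-month assessment at the extreme, or is taken during support and so is not post-intervention. Under the final-session rule its timing depends on need. These figures rest on the Intervention section's durations and on support starting at baseline. With the abstract's 3–4 months the delay is 0–1 month.

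The number affected and the direction and size of any bias cannot be computed. Flexible support is not itself at fault; the problem is that it sets the date of the primary measurement. The point should be corrected, but it does not invalidate the design.

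**What to change.** Collect GSE, K10, RAS-DS, EQ-5D-5L and the service-use questionnaire at 3 months from baseline in every participant, whether or not support has ended. Where no session falls near month 3, use the route already planned for later follow-up, "administered as a questionnaire either through REDCap or a telephone call from study staff". Keep YES and the TFA scale at the end of support, where the plan already puts them: "This measure will be completed during the participant’s final session". Describe the 3-month comparison as the effect of offering flexible support, not strictly as a post-intervention contrast.

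Trial status shows that recruitment began in November 2023, so scores may already have been collected under the final-session rule. Record the actual assessment date and whether support was continuing for every score, so that those taken at a late final session can be identified and analysed by actual time.

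No new visit is needed, but there are costs. Extended participants contribute an on-support score and complete forms on two occasions. The procedure also changes mid-trial at sites already running, and because practices switch in sequence, earlier and later sites may differ in how their 3-month scores were timed. The recorded dates would show any such difference.
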